**Primary outcome**				
Difference in score from the person with dementia between the two arms at six months post-baseline:				
Timed Up and Go (TUG) test [64]	Dynamic balance	Continuous measure of time (in seconds) to complete the task. A cut-off point will not be used because there is no value that can be recommended from existing evidence [48, 49].	In addition to using a stopwatch, performance on the TUG will be measured using a Balance Sensor (THETAmetrix) that contains an accelerometer to digitally record biomechanical movement, and is a small, inexpensive device that is wireless and corrects for tilt dynamically. The data on the device will be downloaded immediately after each test and stored on the researcher’s laptop / tablet and labelled using the participant’s unique ID number.	The TUG is quick and simple to administer in the community [49] and has been recommended for screening for falls risk [50] and assessing gait and balance for preventing falls [51]. While no particular measure of dynamic balance has been recommended in the literature, systematic reviews have identified that the TUG has excellent reliability [42], a strong correlation with falls in retrospective studies [47], is more effective at ruling in falls (0.74 specificity) among individuals classified at high risk of falls [52], and is more suitable with older people who are relatively less healthy and have lower functioning [48]. Devices such as the balance sensor have been shown to produce reliable and valid data for the TUG and its subcomponents [53, 54].
**Secondary outcomes**				
Difference in score between the two arms at six months post-baseline on the following:				
Person with dementia - ×2 balance tests				
Berg Balance Scale (BBS) [55]	The BBS is an objective measure designed to assess functional balance and fall risk in adult populations [55]. The BBS takes an overall assessment of an individual’s balance; “underlying motor systems, static stability, dynamic stability, functional stability limits, anticipatory postural control, and sensory integration” p. 13 [56].	This is a 14 item scale with a 5-point response for each item (0–4), with the sum score used (minimum to maximum possible scores of 0–56, with 0–20 high fall risk, 21–40 medium fall risk, and 41–56 low fall risk).	Total score will be analysed (potential range 0–56) and will be assumed to be interval scaled.	It has been recommended in a recent consensus as one of two core outcome sets for measuring standing balance in adult populations [56]. This consensus reported that this scale would be more useful among those with limited functioning (it is prone to ceiling effects among the generally healthy population) [56]. We chose the BBS for this study based on its likely ease of use among people with dementia, existing published evidence of its suitability for use with people with dementia [36, 57], and its feasibility for use in people’s homes.
Postural sway while standing on the floor and on a foam mat [35]	Static balance under usual and challenging conditions	In both instances, a continuous value will be measured as total (antero-posterior + medio-lateral) normalised path length of the acceleration sway trace of the pelvis during the task. This will be recorded using a Balance Sensor (THETAmetrix), mounted over the upper sacrum (s2 spinous process) to digitally record body sway.	The unit of measurement will be in milli-g/second (mg/s).	The sensor is quick to use (2mins per test) and been shown to be as reliable as laboratory forceplates [58, 59].
Person with dementia – × 4 structured interview scales				

ICEpop CAPability measure for Older people (ICECAP-O) [61]	Quality of life	5 item scale with a 4-point response for each (1–4)	Sum score used (minimum to maximum possible scores of 5–20 with higher scores indicating greater capability). It will be assumed the measure is interval scaled.	This measure is from the perspective of capability to be independent, which is associated with fall risk, general balance and mobility, and sensitive to cognitive status [62]. It is also a measure recommended in guidelines on economic evaluation of fall prevention interventions [63], with results that can be compared with other economic evaluations that used the ICECAP-O.
Carer – ×2 balance tests				
Timed Up and Go (TUG) test [64]	As above	As above	As above	As above
Postural sway while standing on the floor and on a foam mat [35]	As above	As above	As above	As above
Carer – × 2 structured interview scales				
ICEpop CAPability measure for Older people (ICECAP-O) [61]	As above	As above	As above	As above
Zarit Burden Interview (short-form) [65]	Carer burden	12-item scale with a 5-point response for each (0–4)	Sum score used (minimum to maximum possible scores of 0–48 with higher scores indicating greater burden). An assumption will be made that the data are interval scaled.	The most commonly used tool for carer burden [66], and is shorter but just as reliable and valid as the full-length version [65, 66].

Falls measurements will be collected prospectively from baseline until six months post-baseline. These include the number of falls by PWD (count data), the proportion of PWD who have fallen (binary outcome measure), and number of injurious falls (count data). The collection of falls data is in accordance with recommendations made by the Prevention of Falls Network Europe (ProFaNE) [38]. In our trial, the definition of a fall is, “an unexpected event in which the participants come to rest on the ground, floor or lower level” [38]. Falls will be recorded by dyads daily using prospective monthly calendars and returned on a monthly basis by post for data entry. Where falls are reported by dyads or calendars are not returned, a researcher will conduct a telephone interview to collect further information about the fall/clarify missing data. Telephone calls will be conducted weekly with the PWD as recommended for falls data collection with PWD [39]. In addition, to ascertain the accuracy of different recall periods, telephone calls about fall incidents by the PWD will be made monthly with the PWD and every 3 months with the carer. Fall injury will be recorded by telephone interview when recording falls as described above, using an existing set of definitions for severity of injury ([11, 40], p.).

Within the intervention group only, data will be collected half-way through the intervention on a 5-item questionnaire to ask about the importance of features of the intervention such as enjoyment of the classes and confidence in being able to continue to do the home practice. At the end of the final home visit, all dyads will be asked to complete a brief structured exit interview that asks about their hypothetical willingness to pay for the Tai Chi intervention should it be offered in the future as part of routine NHS care. The researcher will also ask participants if there have been any significant changes during the trial to their medical status (e.g. medication usage or elective surgery), which may influence performance on the primary outcome.

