#### Intervention group: Tai chi in addition to usual care

The Tai Chi intervention comprises 3 components: (1) Tai Chi classes, (2) home-based Tai Chi exercises, and (3) a behaviour change component (see logic model in Table 1). The intervention has been designed for participants to accrue 50 h or more of Tai Chi physical activity, because exercise-based interventions to prevent falls are more effective if: they have a higher dosage (50 h or more) and challenge balance (e.g. exercises are conducted while standing) [24]. To allow sufficient time for participants in the intervention condition to be allocated to a class and to complete the 20-week intervention, the post-intervention outcome assessments are scheduled 6 months post-baseline, to coincide with the end of the 20-week intervention period. Information about the Tai Chi exercise prescription and instructional methods are provided in Table 2.

**Table 1 Tab1:** Logic model of the TACIT Tai Chi intervention

Inputs	Activities	Outputs	Impacts	Outcomes

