### Assignment of interventions

In this trial we will aim to achieve equal balance of recruitment of participants between treatment conditions according to the following key prognostic variables: dementia type (due to eligibility criteria, this will be relatively homogenous in this study), age, fall history, and dementia severity. These are important variables because impairment in postural stability will be elevated among those who are older, have fallen in the past 12 months, and present with more severe dementia symptoms [19, 20]. Given that these key prognostic variables are positively correlated [19, 20], only one variable - fall history at baseline: has / has not fallen within the previous 12 months – was selected for a parsimonious and achievable strategy for balancing prognostic factors. The method of allocation needed to accommodate a trial design that allowed for variability in Tai Chi class size according to a dynamic recruitment process. Therefore, to ensure balance within each of the three treatment sites (and across the entire trial), minimisation will be used within each site to achieve a balance in fall history.

For each of the 11–15 classes, once a minimum of 4 dyads in total have been recruited, the dyads will be randomised to the intervention or control group. Random allocation will be achieved using a centralised automatic web-based randomisation system designed and maintained by the UKCRC-registered Peninsula Clinical Trials Unit (CTU). Once a minimum batch of 4 dyads has been recruited within a treatment site, the first dyad will be allocated using simple randomisation and the remaining dyads allocated using minimisation. Afterward, any further dyads recruited into the study before the fifth class has taken place will be randomised individually by minimisation and join the class if so allocated.

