#### Outcome assessor blinding

Baseline measures will be recorded at the PWD’s home before randomisation is performed. After the home visit, dyads will be informed in writing of their treatment arm allocation by staff at the CTU. Given the nature of the intervention, it will not be possible to keep PWD, carers or Tai Chi instructors blind to treatment arm allocation. The researcher who collects baseline data will be kept blind to treatment arm and, in particular, when they conduct the six-month post-baseline follow-up home visit. Participants will be asked at the time of arranging the follow-up visit and at the beginning of the follow-up home visit not to disclose their treatment condition, and to conceal any evidence of participating in class or home-based Tai Chi. After data collection is completed for each follow-up visit, the researcher will make a note of their guess of the treatment arm for the dyad and if dyads accidentally disclose their treatment condition.

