#### Statistical methods

A detailed statistical analysis plan will be finalised separately before follow-up data collection is complete. Participants will be analysed in the group they are randomised to, and (with the consent of participants) we will attempt to collect complete data on everyone and use those data in the analyses. Descriptive statistics will be presented for all baseline outcome data for each trial arm separately. Descriptive statistics will be presented on the following for the PWD and their carer: gender, age, relationship status, current living arrangements, education level, ethnicity, previous experience of Tai Chi and treatment site. Additional descriptive statistics will be presented in relation to PWD: type of dementia, time since diagnosis, other long term conditions, existing injuries, use of a walking aid, number of medications currently taken, falls history (in past 12 months and past month), and current level of physical activity (moderate and vigorous).

Mean TUG scores at 6 months, the primary outcome, will be compared between the two trial arms using a mixed (multi-level) model approach to take into account clustering resulting from the group-based nature of the Tai Chi intervention. Baseline TUG, treatment site, and falls history in the past 12 months (Y/N) will also be included in the model. We will assume that the missing data mechanism is “Missing at Random” (MAR). No imputation methods will be used for the main analysis but will be explored in additional analyses. The method of analysis will be similar for other secondary outcomes for the PWD and carer. In addition, falls count data and the proportion of participants who fell will be analysed using negative binomial and logistic models respectively, taking into account falls history and treatment site. We will also conduct a per protocol analysis that will exclude participants from the Tai Chi group if they received fewer than 50 h (the intended minimum dose of the intervention).

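### Falls are counted from baseline, before randomisation, which dilutes the falls effect toward no difference; the falls models should also state that they account for Tai Chi class.

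*Protocol article*

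**What the plan says.** **Falls window.** The Outcomes section states: "Falls measurements will be collected prospectively from baseline until six months post-baseline". The number of falls, the proportion of fallers and the number of injurious falls are all defined on that window.

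**Order of events.** Under Outcome assessor blinding, baseline measures are taken at the participant's "home before randomisation is performed". Under Assignment of interventions, allocation is triggered by a batch: "once a minimum of 4 dyads in total have been recruited, the dyads will be randomised to the intervention or control group". Later arrivals are handled differently: "any further dyads recruited into the study before the fifth class has taken place will be randomised individually by minimisation".

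**Slack in the schedule.** The intervention section explains why follow-up is at six months for a 20-week course: "To allow sufficient time for participants in the intervention condition to be allocated to a class and to complete the 20-week intervention".

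**Models.** Under Statistical methods, the TUG is compared with a multilevel model that allows for class clustering, and other secondary outcomes are to be handled similarly. Falls then get a sentence of their own: counts and the proportion of fallers "will be analysed using negative binomial and logistic models respectively, taking into account falls history and treatment site". Class is not named there. The Sample size section says that clustering will be considered in the analysis. The section on blinding of data analysis gives the need for class cohort data as the reason for unblinding the statistician.

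**The concern.** A fall before allocation cannot be prevented by the allocated treatment. When such falls count as outcome events, the comparison mixes a period in which the true ratio is 1 with a period in which it may differ from 1, and the estimate moves toward 1. Adjusting for falls history over the previous 12 months does not undo this, because the pre-allocation falls remain in the outcome.

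The trial is partly preparation for a definitive falls trial, so its falls comparison will be read as a signal of promise even though it is secondary and carries no power statement. An understated effect could weigh against the next study.

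The second point is one of consistency. Tai Chi is delivered in classes. The primary model allows for that, but the falls sentence lists its adjustments without class. Read literally, the falls intervals would be too narrow if outcomes within a class are correlated.

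**Working it through.** **1. The plan's own figure.** None is stated for falls. The TUG calculation reproduces. The residual SD is 9.38 × √(1 − 0.7²) = 6.70; with a difference of 4, 60 per group gives 90.04% power (t-based), and 120 / 0.8 = 150. Nothing below changes it.

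**2. Available wait.** Six months is about 26 weeks and the course lasts 20, so about 26 − 20 = 6 weeks lie between baseline and first class. This covers both the wait for randomisation and the wait from randomisation to the first class; the split is not given. Only the first part is at fault, because time after randomisation belongs in the intention-to-treat comparison. Six weeks is therefore an upper bound for the mean pre-randomisation wait if the schedule holds.

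**3. Dilution of the rate ratio.** Assume a constant fall rate, a true ratio of 0.68 throughout the time after randomisation (the pooled rate ratio cited in the Background, for illustration only), and a mean of w weeks counted before randomisation. Then observed RR = 1 − (1 − 0.68) × (1 − w/26). The share of the log effect lost is 1 − ln(RR)/ln(0.68).

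| w (weeks) | Observed RR | Log effect lost |
|---|---|---|
| 1 | 0.69 | 5% |
| 2 | 0.70 | 9% |
| 4 | 0.73 | 18% |
| 6 | 0.75 | 27% |

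**4. Where the mean is likely to lie.** There are 150 dyads over 11 to 15 classes, or 150/15 = 10 to 150/11 = 13.6 dyads per class across both arms. If the batch is the minimum of four and the fourth dyad barely waits, about 3 in 13.6 (22%) to 3 in 10 (30%) wait materially. If those wait 4 weeks (assumed), the mean is 0.22 × 4 = 0.9 to 0.30 × 4 = 1.2 weeks. The observed RR is then about 0.69, with 4% to 6% of the log effect lost. Larger batches would raise this.

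**5. Direction for the proportion of fallers.** Let s be the probability of no fall before randomisation, and a₀ and a₁ the probabilities of no fall afterwards under control and Tai Chi, taken as independent of the earlier period. From baseline, OR = (a₀/a₁) × (1 − s·a₁)/(1 − s·a₀). If Tai Chi works, a₁ > a₀, and this expression rises toward 1 as s falls below 1. So the odds ratio is diluted too; its size would need a fall rate that the protocol does not give.

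**6. What re-windowing costs and gains.** Assume 1 fall per control participant per 26 weeks, negative binomial dispersion 1 and 60 per group. With expected counts m₀ and m₁, the variance of the log ratio is [(1/m₀ + 1) + (1/m₁ + 1)]/60, and power = Φ(|ln RR|/SE − 1.96). With no wait, power is 29%.

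| w | Counted from | m₀, m₁ | SE | RR | Power |
|---|---|---|---|---|---|
| 2 | baseline | 1, 0.705 | 0.271 | 0.70 | 25% |
| 2 | randomisation | 0.923, 0.628 | 0.279 | 0.68 | 28% |
| 6 | baseline | 1, 0.754 | 0.268 | 0.75 | 18% |
| 6 | randomisation | 0.769, 0.523 | 0.295 | 0.68 | 26% |

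Intervals widen by about 3% (0.279/0.271) to 10% (0.295/0.268), but power is higher because the effect is no longer diluted.

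**7. Class ignored.** There are 75/15 = 5 to 75/11 = 6.8 dyads per class, with clustering in the Tai Chi arm only. DE = 1 + (m − 1) × ICC; the ratio of true to naive SE is √((1 + DE)/2); two-sided type I error = 2 × [1 − Φ(1.96/SE ratio)]. This is an approximation for count and binary models.

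| ICC (assumed) | SE ratio | Type I error |
|---|---|---|
| 0 | 1.00 | 5% |
| 0.01 | 1.010 to 1.014 | 5.2% to 5.3% |
| 0.05 | 1.05 to 1.07 | 6.2% to 6.7% |
| 0.10 | 1.10 to 1.14 | 7.4% to 8.4% |

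**The case against.** The strongest reply is that the effect is small and easily handled. Dyads who join after the batch are randomised individually, so only a minority in each class wait long. The dilution is non-differential and conservative. Falls are a secondary outcome with no stated power, and the calendars are kept daily, so the count can be re-windowed at analysis. All of this stands and limits the point, but it does not remove it: the window is stated in the article, and no passage restarts the count at randomisation.

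On clustering, the reply is that the Sample size section promises to consider it without limiting this to TUG, that class data go to the statistician for the analysis, and that falls are listed among the secondary outcomes. This also stands. The falls sentence is out of line with those passages but does not rule class out.

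Some stronger readings are tempting but not supported:
- **The standard error for falls is wrong.** That would require both that class is left out and that the ICC exceeds 0. The documents establish neither.
- **Varying follow-up is ignored and early leavers count as non-fallers.** The article does not say so. Data up to withdrawal may be kept with agreement, and an exposure offset is ordinary detail for the separate analysis plan. In a simulation with equal 20% dropout, the ratio was 0.69 with or without an offset; with unequal dropout the bias could go either way.
- **The wait could average 8 weeks.** That exceeds the roughly 6 weeks of slack.
- **The diluted effect enters the definitive trial's sample size.** The inputs listed for that are the falls rate, the proportion of fallers and the completeness of falls data, not the treatment effect.

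**Conclusion.** The point holds in limited form. As written, the falls window opens before randomisation, so some outcome falls precede allocation and the falls rate ratio and odds ratio are diluted toward 1. With a true ratio of 0.68, the loss runs from about 5% of the log effect at a mean wait of 1 week to 27% at 6 weeks. The low end is more likely. These figures rest on an assumed wait, a constant fall rate and a borrowed ratio.

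The omission of class from the falls sentence is an inconsistency to be aligned, not a proven error. Its possible effect on type I error ranges from none at ICC 0 to about 8.4% at an assumed ICC of 0.10.

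Neither point touches the primary outcome or the sample size. The correction is worthwhile because it is nearly free, not because the trial's main conclusion is at risk.

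**What to change.** - Define the falls observation period in both arms as starting on the date of randomisation. Time from randomisation to the first class stays in.
- Report falls between baseline and randomisation separately, or use them as a baseline covariate.
- Because the window still ends six months after baseline, its length will then vary between dyads. Use log(days observed from randomisation) as the offset in the negative binomial model.
- State that the falls models account for Tai Chi class, in line with the TUG model and the Sample size section.

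The cost is a change of wording. Calendars are daily and randomisation is run through a central web-based system, so no new data are needed. The downside is slightly fewer counted events and slightly wider intervals, about 3% to 10% in the illustration above for waits of 2 to 6 weeks.

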#### Sample size

A formal sample size calculation was undertaken based on detecting a difference in mean timed up and go (TUG) test scores between the intervention and control arms of the study. We found no studies looking at minimum clinically important difference, but did find two studies that had estimated smallest detectable change (i.e. the smallest change that we can be reasonably sure is not measurement error). The two values were 4.09 [41] and 5.88 [37], and we used a conservative value of 4. To find an estimate of standard deviation (SD) for TUG, we found several relevant papers but the values were sensitive to the mix of age and severity of dementia, with one study that seemed to most closely match our population and be based on a reasonable sample size (*n* = 58) [37]. SDs from two different time points were presented (9.74 and 9.01) and we used the average of these (9.38) [37]. In our analysis we will enter baseline TUG as a covariate and assume a correlation of 0.7; test-retest reliability of TUG is excellent [37, 42] but we acknowledge the duration between time points in our study will be longer than prior studies and so we have used a more modest correlation.

Therefore, using a mean difference in TUG of 4, an SD of 9.38, a correlation of 0.7 and a 2-sided 5% significance level, the study will have 90% power when the sample size is 120 (60 per group). Allowing for up to 20% withdrawal / non-completion of outcome measures, we will recruit 150 dyads into the trial (75 per group). These calculations were conducted using nQuery Advisor 7.0. The intervention partly takes place in classes, and there is a possibility of clustering effects. However for the purposes of the sample size calculation we have assumed that these will be negligible, because (a) much of the intervention occurs outside the class environment, and (b) interaction between PWD is not a specific purpose of the intervention’s effect on the primary outcome (only to enhance adherence to the intervention). Clustering effects will be considered in the statistical analysis.

